#### Therapist training and treatment adherence.

Given the complexity of social cognition problems and the presence of behavioral problems, the treatment is delivered exclusively by (clinical) neuropsychologists who engage in frequent peer consultation sessions to ensure consistent and high-quality application of the T-ScEmo protocol. Treatment adherence will be monitored using a checklist, where the therapist logs completed components and homework. Deviations or additions will be noted. Adherence percentages will be calculated based on session content and homework completion.

#### Ethics and dissemination.

The Ethics Review Committee Psychology and Neuroscience of Maastricht University provided ethical approval for the study (date 12-17-2024, reference number 289_121_12_2024). Additionally, the study protocol has been reviewed and approved by the institutional ethical committee (Commissie Wetenschappelijk Onderzoek) of GGZ Oost Brabant (date 12-24-2024, ref. 06.809/5315). All patients and their significant others will provide written informed consent prior to participation. Ethical and safety considerations are integrated throughout the study design, with particular attention to the inclusion of potentially vulnerable individuals with ABI and neuropsychiatric problems. Confidentiality of participant data will be ensured through secure data storage and pseudo-anonymization procedures (i.e., coding) with applicable data protection regulations.

The results of the study will be disseminated through peer-reviewed international publications, conference presentations, and stakeholder meetings. In addition, de-identified datasets and accompanying documentation will be made available in an open-access research data repository to facilitate transparency and replication. The study will be reported in accordance with the Single-Case Reporting guideline In Behavioural Interventions (SCRIBE; [53]), ensuring clarity and completeness in reporting.

### Participants

The goal is to include at least 8 patients receiving treatment at the Center of Excellence for Brain Injury and Neuropsychiatry (GGZ Oost Brabant), providing in- and outpatient care for patients with neuropsychiatric problems following ABI. The most common neurological diagnoses in this setting include stroke (ischemic, hemorrhagic, including subarachnoid hemorrhage), TBI, post-anoxic encephalopathy, brain tumors, and infections such as meningitis. Eligibility will be assessed for both clinical and outpatient populations.

Participants will be individuals with an established and documented history of ABI and current neuropsychiatric problems. These neuropsychiatric problems are broadly defined to include a wide range of behavioral problems, regardless of whether they meet formal DSM-5 criteria, that warrant referral and admission to our institution. As such, patients presenting with behavioral problems such as aggression, impulse control problems, disinhibited behavior, compulsion, and apathy are eligible for inclusion, even in the absence of a DSM-5 classification. In this study, patients present with neuropsychiatric problems of such severity and complexity that treatment within a specialized neuropsychiatric setting is indicated. These patients differ from those commonly seen in standard rehabilitation settings, who may also present with social cognition deficits, but exhibit less severe and disruptive neuropsychiatric symptoms.

For each participating patient, a significant other will also be included in the study. Ideally, this is the patient’s life partner, however, when no partner is available, a close family member (e.g., parent or sibling) or a close friend may fulfill this role. The significant other provides valuable information about the patient, their relationship, and their own experience related to the patient’s condition, and can also support the patient throughout the treatment.

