**Methods and analysis:**

A non-concurrent, randomized, multiple-baseline single-case experimental design (SCED) will be employed to investigate the effectiveness of T-ScEmo in this study. At least 8 participants and a significant other will be randomly assigned to one of three baseline lengths. The primary outcome measures (social functioning, neuropsychiatric problems, relationship quality) will be assessed daily during baseline and twice a week during the treatment and maintenance phases. Secondary outcomes will be assessed at T0 (pre-treatment), T1 (post-treatment), and T2 (1-year follow-up). Both patients and the significant other will complete all outcome measures.

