Although the effectiveness of T-ScEmo has been demonstrated in individuals with TBI, it remains unknown whether the treatment is also effective in individuals with ABI and comorbid neuropsychiatric problems. Therefore, the primary aim is to examine the effect of T-ScEmo on social functioning in patients with ABI and comorbid neuropsychiatric problems (RQ1). Secondary aims include examining the effects of T-ScEmo on neuropsychiatric problems and quality of partner relationships in this population (RQ2).

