#### Secondary research questions (RQ2).

In addition, we hypothesize that T-ScEmo will reduce neuropsychiatric problems in patients with ABI and comorbid neuropsychiatric problems. Social cognition problems often co-occur with, and in some cases contribute to, with neuropsychiatric symptoms following acquired brain injury (ABI). These social cognition difficulties are also commonly observed in other psychiatric disorders such as autism spectrum disorders and schizophrenia [8,37]. Although our study focuses on patients with ABI, improvements in social cognition have the potential to alleviate distress and behavioral dysregulation associated with neuropsychiatric symptoms across different conditions [28].

Finally, we hypothesize that the quality of partner relationships will improve. Involving a partner in the treatment may increase mutual understanding and support, while better social responsiveness on the part of the patient can positively influence relationship quality.

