** *Partner relationship* **							
Relationship Quality Scale (RQS)	Perceived quality of relationship with significant other	▲	▲ (daily)	▲ (twice a week)		▲ (twice a week)	▲
Dutch Marital Satisfaction and Communication Questionnaire (DMSCQ) [48]	Marital satisfaction, negative communication and open communication	▲			▲		▲

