** *Partner relationship* **							
Relationship Quality Scale (RQS)	Perceived quality of relationship with significant other	▲	▲ (daily)	▲ (twice a week)		▲ (twice a week)	▲
Dutch Marital Satisfaction and Communication Questionnaire (DMSCQ) [48]	Marital satisfaction, negative communication and open communication	▲			▲		▲

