#### In- and exclusion criteria.

The in- and exclusion criteria are largely consistent with those outlined in the T-ScEmo4ALL treatment protocol [54]. A key deviation, however, is that patients with comorbid neuropsychiatric problems are not excluded from participation. Accordingly, individuals with ABI and co-occurring neuropsychiatric problems are eligible for inclusion in this study. Inclusion criteria are presented in Table 2. This table is adapted from Heegers et al. [54].

**Table 2 pone.0358008.t002:** Overview of inclusion and exclusion criteria T-ScEmo4ALL Plus^+^.

Inclusion criteria patient	Inclusion criteria significant other	Exclusion criteria
Presence of social cognitive impairments, (i.e., impairments in emotion recognition, ToM, or social behaviour>1 of 4 tests indicative and/or>1 of the (sub)scales of relevant questionnaires indicative and/or, if available, the presence of frontal lesions on CT or MRI), judged by a neuropsychologist	Preferably a life partner. If a life partner is not available, a family member or close friend	Serious neurodegenerative conditions interfering with treatment
Presence of a neurological disorder (i.e., stroke, brain tumor, TBI, infections, post-anoxic encephalopathy)	Chosen by patient	Incapacity to make informed choices, to be judged by the neuropsychologist
Presence of current neuropsychiatric problems (i.e., aggression, impulse control problems, disinhibited behavior, compulsion, and apathy)	Age > 18	Serious cognitive disorders (aphasia, amnesia, disorders in visuoperception) interfering with treatment, to be judged by a neuropsychologist
Chronic state (6 months post-injury) to minimize the influence of spontaneous recovery		No significant other available who can fill out the questionnaires
Age between 18 and 70 years of age		Not able to speak and understand the Dutch language

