#### Statistical analyses.

Statistical analyses of SCED data have gained prominence in recent years and will be used as a complementary method of data evaluation. There are still, however, no agreed-upon criteria for statistical analysis of SCED data [60]. Data from the frequently administered measures will be displayed and analyzed using the Shiny app for Single-Case Data Analysis [57]. The generated graphs will support visual analysis, and regression analysis will be conducted for quantitative assessment. Randomization tests (RTcombiP; [61]) will be applied to evaluate if levels of social cognition problems, social communication, social interaction, social problems, and neuropsychiatric problems differ significantly between phases (baseline versus treatment + follow-up).

If visually analysis yields strong or moderate evidence, effect size estimates will be calculated using non-overlap of all pairs (NAP) for the dependent variables: social cognition problems, social interaction, social communication, neuropsychiatric problems, and neuropsychiatric problems. To assess individual improvements on the periodic measurements (BAFQ, DEX, IRI, FEEST, Cartoon test, LCQ, DMSCQ, NPI-Q), the Reliable Change Index (RCI) will be calculated. The RCI will indicate whether post-treatment and follow-up changes are both statistically and clinically significant.

Reporting of the study will follow the Single-Case Reporting guideline In Behavioral interventions (SCRIBE) checklist [53], consisting of 26 items that outline the structure of a SCED report.

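### The relationship part of RQ2 is about partners, but non-partner dyads are scheduled for the marital questionnaire and can count towards the conclusion

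*Protocol article*

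**What the plan says.** Four parts of the protocol article bear on this point.

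- **Aim and hypothesis.** The last paragraph of the Introduction makes partner-relationship quality part of RQ2. Under Secondary research questions the authors write that "we hypothesize that the quality of partner relationships will improve", and the reason given is that a partner takes part in the treatment.
- **Who the significant other is.** Table 2 reads "Preferably a life partner. If a life partner is not available, a family member or close friend". The Participants section says the same: the life partner is the ideal, and failing that "a close family member (e.g., parent or sibling) or a close friend may fulfill this role".
- **What is measured.** Under its heading for partner relationship, Table 1 lists two instruments for both patients and significant others. The DMSCQ, described as "Marital satisfaction, negative communication and open communication", is taken at T0, T1 and T2. The RQS, described as perceived quality of the relationship with the significant other, is taken repeatedly across the phases. Neither row or footnote limits an instrument to partner dyads.
- **How it is analysed.** The Statistical analyses section computes the reliable change index (RCI) for the periodic measures "BAFQ, DEX, IRI, FEEST, Cartoon test, LCQ, DMSCQ, NPI-Q", with no subset for the DMSCQ. The Visual analyses section grades the evidence on the frequently administered measures by counting demonstrations of effect and of no effect.

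**The concern.** The hypothesis is about partners, the sample is not limited to partners, and neither the schedule nor the analysis separates the two kinds of dyad. A mother or friend who follows Table 1 is asked about marital satisfaction, and the answer is then tested for reliable change. If such raters skip the form instead, the DMSCQ result rests on a subset that the article never declares.

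The RQS raises a different problem. Its scores are sound, but they sit under the partner heading, so a friend's ratings can become evidence on partner relationships.

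What is at stake is the reading of one secondary conclusion in a study of 8 to 20 dyads, where a single dyad can change the evidence grade.

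**Working it through.** The plan gives no figure to reproduce here. The check is a comparison of the passages, with a small calculation for scale.

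**1. Which measures are affected**

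| Measure | Construct in Table 1 | Partner dyad | Non-partner dyad |
|---|---|---|---|
| DMSCQ | Marital satisfaction and communication | Fits RQ2 | Does not measure the RQ2 construct |
| RQS | Relationship with the significant other | Fits RQ2 | Valid score, but not a partner relationship |
| NPS, NPI-Q | Neuropsychiatric problems | Unaffected | Unaffected |

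**2. Weight of the DMSCQ.** Relationship quality is in neither the list of outcomes for the randomization tests nor the list for NAP. The NAP list names neuropsychiatric problems twice, so one entry may be a slip. As the text stands, the RCI on the DMSCQ is the only statistical analysis that names a relationship measure. The RQS falls under the general visual and regression analysis of frequent measures.

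**3. Effect on the evidence grade (RQS only).** Strong evidence needs at least three demonstrations and none of no effect. Moderate evidence needs at least three with at least one of no effect. Fewer than three is no evidence. Counting one demonstration per dyad (my reading), two invented cases with 8 dyads show the range:

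- Three non-partner dyads improve and five partner dyads do not. All dyads: three demonstrations and five of no effect, so moderate. Partner dyads only: none of five, so no evidence.
- Seven partner dyads improve and one friend dyad does not. All dyads: moderate. Partner dyads only: strong.

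**4. How likely a non-partner dyad is.** The article gives no share, so let p be an assumed share, with dyads independent. For n dyads, P(at least one) = 1 − (1 − p)^n. With n = 8 and p = 0.10 this is 1 − 0.90^8 = 0.570. With p = 0.30 it is 1 − 0.70^8 = 0.942.

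| Assumed p | P(at least one), n = 8 | P(at least one), n = 20 | Expected partner dyads of 8 = 8(1 − p) | P(fewer than 3 partner dyads of 8) |
|---|---|---|---|---|
| 5% | 0.337 | 0.642 | 7.6 | 0.0000 |
| 10% | 0.570 | 0.878 | 7.2 | 0.0000 |
| 20% | 0.832 | 0.988 | 6.4 | 0.0012 |
| 30% | 0.942 | 0.999 | 5.6 | 0.0113 |
| 40% | 0.983 | 1.000 | 4.8 | 0.0498 |
| 50% | 0.996 | 1.000 | 4.0 | 0.1445 |

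The last column is the binomial probability of 0, 1 or 2 partner dyads among 8. It uses three because the Sample size section calls replication across at least three participants essential. A restriction to partner dyads would seldom breach that minimum unless about half the dyads were non-partner.

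**The case against.** The strongest reply is that no sentence says a friend must complete a marital questionnaire. Table 1 lists instruments by role, and a condensed article may leave a not-applicable rule to the full protocol. The Abstract's statement that "Both patients and the significant other will complete all outcome measures" cannot close that gap. Table 1 gives the IRI, FEEST and Cartoon test to patients only and the NPI-Q and CSI to significant others only, so the sentence is not literal. A non-partner is also the fallback, and marital status is recorded at T0, which would help to sort the dyads later. These points stand, and the Abstract sentence should carry no weight here. But eligibility, schedule, hypothesis and RCI are each stated in the article, and they do not fit together whether the form is completed or skipped.

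Three stronger readings are tempting, and the article does not support them.

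- **That non-partner scores dilute the partner result.** The RCI assesses individual improvement case by case, and no pooled DMSCQ estimate is described. Only a summary across cases can mix the two kinds of dyad.
- **That RQS scores from non-partners are invalid.** The scale is worded for any significant other. The fault lies in counting these scores towards a partner conclusion.
- **That the DMSCQ could fall short of the three demonstrations required.** That rule governs visual analysis of the frequent measures, not the RCI.

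**Conclusion.** The point holds for the relationship half of RQ2. DMSCQ change scores from non-partner dyads would not measure partner-relationship quality, and RQS series from those dyads could shift the evidence grade in either direction. RQ1, the neuropsychiatric half of RQ2 and partner dyads' own RCI results are not touched.

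The size depends on a share that the article does not give. The mismatch is likely to arise at 8 dyads unless nearly all significant others are partners: 57% at an assumed share of 10%, and still 34% at 5%. If no non-partner dyad enrols, the problem does not arise. It is worth correcting because it changes what the study can conclude about partners.

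**What to change.** - Administer and analyse the DMSCQ only in dyads whose significant other is the life partner.
- Rest the partner-relationship conclusion, from both DMSCQ and RQS, on those dyads, and state their number beside the result.
- Report RQS from the other dyads separately, labelled as relationship with the significant other.

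This takes a sentence or two in the analysis section and a filter on the digital questionnaires. The Procedure section has recruitment running to the end of December 2026, and under Blinding the investigator analyses nothing until data collection is complete. The rule can therefore be set before results are seen.

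The price is fewer dyads behind the partner-relationship conclusion: an expected 5.6 to 7.2 of 8 at assumed non-partner shares of 30% to 10%, with about a 1% chance or less of falling below three. A patient whose partner exists but cannot take part would also be left out of that conclusion. This is consistent with the hypothesis, which relies on the partner being involved.

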#### In- and exclusion criteria.

The in- and exclusion criteria are largely consistent with those outlined in the T-ScEmo4ALL treatment protocol [54]. A key deviation, however, is that patients with comorbid neuropsychiatric problems are not excluded from participation. Accordingly, individuals with ABI and co-occurring neuropsychiatric problems are eligible for inclusion in this study. Inclusion criteria are presented in Table 2. This table is adapted from Heegers et al. [54].

**Table 2 pone.0358008.t002:** Overview of inclusion and exclusion criteria T-ScEmo4ALL Plus^+^.

Inclusion criteria patient	Inclusion criteria significant other	Exclusion criteria
Presence of social cognitive impairments, (i.e., impairments in emotion recognition, ToM, or social behaviour>1 of 4 tests indicative and/or>1 of the (sub)scales of relevant questionnaires indicative and/or, if available, the presence of frontal lesions on CT or MRI), judged by a neuropsychologist	Preferably a life partner. If a life partner is not available, a family member or close friend	Serious neurodegenerative conditions interfering with treatment
Presence of a neurological disorder (i.e., stroke, brain tumor, TBI, infections, post-anoxic encephalopathy)	Chosen by patient	Incapacity to make informed choices, to be judged by the neuropsychologist
Presence of current neuropsychiatric problems (i.e., aggression, impulse control problems, disinhibited behavior, compulsion, and apathy)	Age > 18	Serious cognitive disorders (aphasia, amnesia, disorders in visuoperception) interfering with treatment, to be judged by a neuropsychologist
Chronic state (6 months post-injury) to minimize the influence of spontaneous recovery		No significant other available who can fill out the questionnaires
Age between 18 and 70 years of age		Not able to speak and understand the Dutch language

### Intervention

T-ScEmo is an evidence-based, multifaceted treatment protocol designed to improve social cognition and emotion regulation in patients with ABI. T-ScEmo is part of standard clinical practice in the Netherlands and has been implemented at the Center of Excellence for Brain Injury and Neuropsychiatry since 2024, constituting ‘care as usual’. It is included in the Dutch guideline for neuropsychological rehabilitation [55], which recommends T-ScEmo as the preferred intervention for addressing deficits in social cognition. The T-ScEmo treatment is thus recommended by leading experts in clinical neuropsychology.

T-ScEmo treatment comprises 20 one-hour sessions and is structured into extended psychoeducation (for both patient and the significant other) followed by 3 core modules: emotion perception (module 1), perspective taking and understanding social information (module 2), and goal-directed social behavior (module 3). These modules are designed to be interdependent and mutually reinforcing, therefore, the developers strongly recommend delivering the full protocol. The presence of a significant other is required in the first psycho-education session and during the third module. Modules 1 and 2 follow a fixed structure across 10 sessions, while module 3 allows for tailoring based on individual needs and personal goals. Each session follows a consistent format: (1) review of homework assignments (5–10 minutes), (2) presentation and practice of new material, i.e., content of the session (45–50 minutes), and (3) preview of the next session with new homework assignments (5 minutes). Therapists familiar with the T-ScEmo are expected to require around 15 minutes of preparation time per session (printing documents, reviewing content). An overview of the treatment sessions, content and practical information is presented in Table 3. This table is adapted from Heegers et al. [54].

**Table 3 pone.0358008.t003:** Content of T-ScEmo protocol and practical information.

**T0 – BASELINE MEASUREMENTS**	Neuropsychological tests: face to face Questionnaires: digital Setting treatment goals
**PSYCHO-EDUCATION**	
Session 1**	Explanation of findings following the neuropsychological assessment and psycho-education
**MODULE 1**	**Perceiving social information**
Session 2	Perceiving emotional facial-features
Session 3	Facial-features and mimicry
Session 4	Facial-features and personal emotional experiences
Session 5	Perceiving and recognizing disapproval and shame
Session 6	Perceiving and recognizing corrective emotions, such as shame and disapproval/discomfort
**MODULE 2**	**Understanding social information**
Session 7	Thoughts, feelings, and behaviour of the other
Session 8	Perspective taking
Session 9	Empathy
Session 10	Complex social information: contradiction
Session 11*	Interim evaluation
**MODULE 3**	**Regulating behaviour in social situations**
*Note:*	*Module 3 includes several optional components. A total of 9 sessions may be devoted to Module 3. The selection of sessions is based on the participant’s goals*
Session 12	Personal space
Session 13*	Listening skills, turn-taking and timing
Session 14*	Checking emotions and thoughts of the other
Session 15	Training in social problem-solving
Session 16a	Understanding behaviour: registration
Session 16b	Social contacts: initiating and restoring contact
Session 17a	Understanding behaviour: registration of anger
Session 17b	Social contacts: appreciating & strengthening
Session 18*	“Inappropriate” behaviour and correcting feedback
Session 19a	Behaviour in stressful situations I (time-out + cue card)
Session 19b	Behaviour in stressful situations II (apologizing)
Session 20	Treatment evaluation
**T1 – POST-TREATMENT MEASUREMENTS**	Neuropsychological tests: face to face Questionnaires: digital
**T2 – FOLLOW-UP MEASUREMENTS**	Neuropsychological tests: face to face Questionnaires: digital

* Presence of a significant other is *desirable.*

** Presence of a significant other is *necessary.*

